### Sample size

We hypothesise patients in the ISDM group to reach higher adherence to prescriptions of antihypertensive and statin medication.

Based on current DMP-data [39] and the preliminary results of the pilot RCT [35], we assume that approx. 60% of patients in the control group will adhere to the choice. We estimate that more than 80% of patients in the intervention group will adhere.

We calculate the sample size providing 80% power to detect an absolute difference of 20% between the intervention and the control group, using Fisher’s exact test at the 5% level of significance. Thus, in a non-cluster RCT data on about 90 patients per group (180 participants) would need to be included in data analysis.

Since observations on individuals in the same cluster tend to be non-independent, the effective sample size is less than the total number of individual participants. The reduction in effective sample size depends on the average cluster size (m) and the degree of correlation within clusters (intracluster correlation coefficient, ICC). To retain power, the sample size should be multiplied by the so-called design effect (DE = 1 + (m - 1) × ICC) [36]. However, we did not identify data, allowing an estimation of a probable ICC for the primary endpoint used in our study. Krones et al. [28] reported an ICC of 0.06 for an endpoint relating to patient participation. Branda et al. [63] published an ICC of 0 or nearly 0 for knowledge, decisional comfort, and medication adherence. Thus estimating an ICC of 0.03 and a mean cluster size of 13 participants, we calculate with a design-effect of DE = 1.36. Hence, data on 122 patients per study arm (total 244 participants) need to be included in data analysis. Estimating a drop-out rate of about 20%, 306 participants will be recruited for randomisation, distributed across 24 clusters (practices). This power calculation was conducted by [name] Biostatistician (Jena, Germany).

### Process evaluation

The effectiveness of the ISDM programme may depend on the complex interaction between components (e.g. provider training module and educational strategies) and conditions of the setting.

Based on the framework by Grant et al. [64], the underlying processes involving clusters and patients will be monitored to explore barriers and promoting factors of the implementation of the intervention programme. Field exploration has indicated possible barriers regarding extra workload and high organisational efforts. Telephone interviews with MAs of the intervention group will be conducted after all patients attended the teaching sessions. Interviews will focus on possible barriers in the implementation of the teaching module, organisational aspects, and team collaboration. At the end of the study, interviews with the GPs will be conducted to assess the perceived effort for the practices.

The standardised telephone interviews will be used to assess the primary endpoint. The interviews will also focus on barriers of adherence and treatment effort perceived by the patients. To avoid that they feel kept under surveillance and to avoid socially desirable answers, questions regarding statin adherence will be embedded into more general questions e.g. on individual treatment effort. All interviews will be recorded and qualitatively analysed. Results will be used to plan the optimisation of implementation concept.

### Ethical approval

The study protocol was approved by the ethics committee of the University Hospital Jena and the Medical Council of the Free State of Thuringia. Written participant information about study objectives and procedures are given to eligible patients. Standardised forms are used to document informed consent.

### Confidentiality

In order to maintain data privacy, pseudonyms are used to combine data sets (baseline and follow-up data) and to identify data if patients withdraw informed consent. The pseudonym list of practices in the Free State of Thuringia is kept under lock at the University Hospital Jena, the list of practices in Hamburg at the Unit of Health Sciences and Education of the University of Hamburg.

## Discussion

In this cRCT, a novel SDM intervention will be compared with usual care in the setting of primary diabetes care.

The study has several strengths. The intervention is intended to promote the implementation of current guideline recommendations into practice, by systematically guiding patients together with their healthcare providers to deliberate on options and to set individual treatment goals in terms of SDM [1,8,20]. Patient teaching module and provider training are brief in their duration, which simplifies implementation into practice. Preliminary studies [32,33,35] have indicated good acceptance and feasibility.

The study has limitations. Firstly, it is impossible to keep the practices blind. At a kick-off symposium MAs and physicians have received information on the innovative ISDM approach to motivate them for participation in the study. Secondly, cluster designs in particular are susceptible for selection bias. This problem will be addressed by recruiting patients before randomisation. Thirdly, since it is not feasible to reliably assess SDM in the context of this study, we decided to use adherence to prescribed medication as an indirect measure. Similar to SDM, adherence is a behaviour influenced by subjective norms such as perceived attitudes of other individuals. Self-report can be biased by socially desired answers and pill count as a more objective measure is not feasible within this study. In order to avoid interfering with the intervention we will not assess self-reported adherence at baseline. Rather, medication prescriptions will be used as a surrogate to evaluate comparability of groups at baseline.

Fourthly, in order to reduce complexity we focused on the most relevant cardiovascular complication in type 2 diabetes, i.e. myocardial infarction. However, prevention requires a holistic approach. Issues such as stroke or microvascular complications are already addressed in the standard treatment and teaching programmes within the DMP, without however including numerical and comparative risk information. In order to communicate benefits and harms of blood glucose and blood pressure control we used UKPDS data [5,52] on the combined endpoint *any diabetes-related endpoint* which also includes other cardiovascular outcomes.

At the end of this study, information on the effectiveness of the ISDM programme and on processes that interfere with or promote a successful implementation into primary care practices will be available.

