### Randomisation and blinding

Randomisation of practices will be performed after patient recruitment and retrieval of baseline data. To ensure close balance of entities in each group, randomisation will be performed in blocks of 4. The randomisation sequence will be generated by the Centre for Clinical Studies at the University Hospital Jena. Blinding of practices that deliver the intervention programme is not feasible. However, they will be asked to keep the allocation blinded as far as possible, i.e. to not reveal study details to the patients. Patients will be informed that the objective of the study is to compare two different approaches to better acknowledge patients’ preferences and values in decision making on preventive measures and that they have an equal chance of receiving the intervention or the control programme. Allocation concealment will be ensured for database entry and statistical analyses.

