### Data collection

Patient records and standardised forms will be used to collect baseline characteristics and outcome data. Outcome data is documented electronically as scheduled in the DMP.

Baseline characteristics include age, gender, first-language (usually spoken at home), educational status, body mass index (BMI), smoking status, blood pressure, LDL-cholesterol level, total cholesterol level, HbA1c level, current medication, and previous participation in diabetes and hypertension patient education programmes. Individual baseline risks of myocardial infarction are calculated by using a risk assessment tool. The tool uses age, smoking status, and clinical parameters and is derived from the Framingham function calibrated [61] to the average heart attack risk in the German population.

The treatment goals set by the individual patient in the ISDM group will be assessed after the teaching session and after the consultation by extracting them from the documentation sheet. Treatment goals of the control group will be assessed at a practice visit by using a standardised documentation form.

Telephone interviews will be conducted to assess the adherence to the current drug prescriptions. A standardised interview guide will be developed including questions such as *“Patients with diabetes often need to take several pills. I am interested in your current use of pills. Could you tell me, which medication boxes do you use? Which substances are labelled on the boxes?”*, and “*Have you ever missed any pills in the past seven days?”* [62]*.* Patients are classified as non-adherent if their answers are inconsistent with the prescriptions. Patients without antihypertensive prescription will be asked about statin medication. Patients with neither antihypertensive nor statin prescription will not be included in data analysis for the primary endpoint. In order to avoid socially desirable answers, the interviews will be conducted by a study assistant of the study organising centre, independent from the practices and blinded towards the allocation. Interviews will be audio-taped. In ambiguous cases, the tape will be analysed by a project member who is also blinded toward patients’ allocation. Inter-rater consensus will be achieved by discussion. Cholesterol levels at baseline and follow-up will be used to validate data on adherence to statin choice.

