#### Primary outcome

Fisher’s exact test will be used to compare the groups regarding the adherence to antihypertensive or statin therapy.

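### The primary Fisher's exact test ignores the practice clustering that the sample size allows for, and leaves the baseline prescriptions already collected unused; the first is the main repair, the second a small gain in precision

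*Protocol article*

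**What the plan says.** All references are to the protocol article.

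- **Primary outcome:** "Fisher’s exact test will be used to compare the groups regarding the adherence to antihypertensive or statin therapy". Neither a covariate nor a term for practice is named here or elsewhere under Data synthesis.
- **Sample size:** planning rests on the same test at a 5% level, "providing 80% power to detect an absolute difference of 20% between the intervention and the control group". It then multiplies by a design effect of 1.36 because patients within a practice are correlated.
- **Randomisation and blinding:** practices are allocated after patients are recruited and baseline data retrieved, and "randomisation will be performed in blocks of 4". No stratification factor is stated.
- **Data collection:** the baseline list includes age, gender and, among others, "LDL-cholesterol level, total cholesterol level, HbA1c level, current medication". The endpoint concerns antihypertensives first; statins are asked about only where no antihypertensive is prescribed. "Patients with neither antihypertensive nor statin prescription will not be included in data analysis for the primary endpoint".
- **Discussion (limitations):** to avoid interfering with the intervention, "we will not assess self-reported adherence at baseline". Instead, "medication prescriptions will be used as a surrogate to evaluate comparability of groups at baseline". Nothing is said about what follows if the groups turn out not to be comparable.

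**The concern.** Leaving out a baseline adherence interview is a reasoned choice. The difficulty is the test that follows. A 2×2 Fisher test treats the analysed patients as independent, although only 24 practices are randomised and the sample size itself assumes that patients within a practice are alike. It also cannot take a covariate, so whatever the comparability check shows, the stated primary analysis has no means of acting on it.

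Two things are at stake, of unequal weight:

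1. **Validity of the test.** Ignoring clustering understates the standard error and raises the false-positive rate.
2. **Precision.** Few randomised units and no stated stratification make chance imbalance between arms larger than in an individually randomised trial of the same size. If prescriptions predict adherence, that imbalance stays in the realised estimate. There is a plausible mechanism: patients count as non-adherent when their answers do not match their prescriptions, so more drugs give more chances of a mismatch. The protocol gives no figure for the strength of this link.

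Without a pre-specified rule, a decision to adjust could also be taken after the comparability table has been seen.

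**Working it through.** **1. The plan's own figures.** Inputs from Sample size: 60% against 80% adherence, 80% power, 5% level (sides not stated; two-sided fits), ICC 0.03, mean cluster size 13, drop-out 20%, 24 practices.

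- Exact two-sided Fisher power is 0.796 at 89 per arm and 0.802 at 90, which agrees with the stated 90.
- Design effect: 1 + (13 − 1) × 0.03 = 1.36. Then 90 × 1.36 = 122.4, stated as 122 per arm (244).
- Drop-out: 244/0.8 = 305, or 122/0.8 = 152.5, rounded up to 153 per arm, giving 306.

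The sample size reproduces. The fault lies in the analysis, which does not carry the clustering forward.

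**2. Effect of ignoring clustering.** Simulation under the null: 24 practices, 10 analysed patients each (244/24 = 10.2), 70% adherence in both arms, 3,000 runs per setting, with a baseline covariate shifting adherence by 0, 10 or 20 points. Rejection rates at the nominal 5% level:

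| Outcome ICC | Fisher | Cluster-level t-test, unadjusted | Cluster-level t-test, adjusted |
|---|---|---|---|
| 0 | 3.6% to 3.9% | 5.0% to 5.8% | 5.1% to 5.6% |
| 0.03 | 5.9% to 6.5% | 5.0% to 5.1% | 4.9% to 5.3% |
| 0.06 | 8.7% to 10.0% | 4.7% to 5.5% | 4.7% to 5.3% |

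Simulation error near 5% is about ±0.8 points. With no covariate effect at all, Fisher's rate is already 5.9% at ICC 0.03 and 8.7% at 0.06. The inflation therefore comes from the clustering, and adding a covariate alone would not cure it. The protocol plans with 0.03 and quotes 0.06 from another trial's patient-participation endpoint. It also quotes an ICC at or near 0 for outcomes that include medication adherence; at 0, Fisher's test is conservative.

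**3. Chance imbalance in a baseline factor.** The documents give neither the prevalence of any prescription factor nor its link to adherence. Assumed: prevalence p = 50%, covariate ICC 0.03, link of 10 to 20 points.

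- Design effect for the covariate at the analysed cluster size: 1 + (122/12 − 1) × 0.03 = 1.275.
- SD of the between-arm imbalance: √(2 × p(1 − p) × DE/122) = √(2 × 0.25 × 1.275/122) = 0.072, or 7.2 points. With individual randomisation (ICC 0) it is 6.4 points; with covariate ICC 0.10 it is 8.9.
- SD of the resulting shift in the estimate: 7.2 × 0.10 = 0.7 points and 7.2 × 0.20 = 1.4 points. The simulated standard error of the treatment difference at ICC 0.03 is about 6.6 points.
- Unfavourable case: a 2-SD imbalance with a 20-point link shifts the estimate by 2 × 7.2 × 0.20 = 2.9 points (3.5 at covariate ICC 0.10), against the 20-point target.
- Lower prevalence, p = 15%: SD = √(2 × 0.1275 × 1.275/122) = 5.2 points.

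**4. What adjustment gains.** With average adherence 70% (variance 0.21):

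- R² = 0.25 × 0.10²/0.21 = 1.2%, and 0.25 × 0.20²/0.21 = 4.8%.
- Standard error ratio √(1 − R²) = 0.994 and 0.976, a reduction of 0.6% to 2.4%.
- Power by the normal formula at 122/1.36 = 89.7 effective patients per arm: 83.8% unadjusted, about 84.2% to 85.6% adjusted. (It exceeds 80% because this formula lacks Fisher's conservatism.)
- Simulated power of the cluster-level tests with a 10-point link: 84.4% unadjusted, 84.8% adjusted, a difference within simulation error (about ±1.3 points).
- Simulated mean effect in that setting, true value 20 points: 20.2 unadjusted, 20.0 adjusted. Under the null both average about 0.

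**The case against.** The strongest reply is that an unadjusted comparison after randomisation is valid. Chance imbalance is part of sampling error, a test that respects clustering already covers it, and adjustment is an option for precision that an analysis plan may settle. All of this stands except the last step. The article names the primary test, and a Fisher test can take neither a covariate nor a cluster term, so this is a stated choice and not a detail left open.

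Three stronger readings are tempting and are not supported:

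- **That the unadjusted estimate is biased.** It is not, over randomisations. The 3-point figure above is a shift given one unlucky allocation.
- **That the protocol treats prescriptions as a proxy for each patient's baseline adherence.** It calls them a surrogate for judging whether the groups are comparable, and gives no link to adherence.
- **That imbalance threatens the result.** The figures rest on assumptions towards the upper end. A prevalence of 50% maximises p(1 − p), and a 20-point link is as large as the whole target effect.

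Two objections bear on the choice of covariates. Having any prescription at all would vary little in the analysed set, because patients with neither drug are left out. A baseline statin prescription does not identify which drug class is assessed, since that depends on whether an antihypertensive is prescribed. Pooling the two classes is a declared definition of the endpoint and is not itself an error.

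**Conclusion.** The point holds in two parts of unequal weight. The main one is that the primary test ignores the clustering for which the sample size pays. Simulated type I error is about 6% at the planned ICC of 0.03 and 9% to 10% at 0.06, with no inflation if the ICC is truly 0. The minor one is that baseline prescriptions are collected but serve only to describe comparability. Under assumed values with no source in the documents, the resulting shift has an SD of about 0.7 to 1.4 points against a standard error of about 6.6, and adjustment trims that error by 0.6% to 2.4%. On its own the covariate would be a refinement; it is worth adding because the analysis has to be rewritten anyway.

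**What to change.** Replace Fisher's test for the primary endpoint with a practice-clustered analysis suited to 24 clusters: a cluster-level analysis, or GEE or a mixed model with a small-sample correction. Report a marginal risk difference, so that the estimate matches the 20-point difference in the sample size and does not become a conditional odds ratio.

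Pre-specify a short list of T0 covariates:

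- any antihypertensive prescription (yes/no), which approximates the drug class assessed;
- number of antihypertensive drugs;
- age and sex, optional.

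T0 class is only an approximation, because Table 2 takes the endpoint's prescriptions at T3. Do not adjust for T3 prescriptions, even so: the Objectives expect the programme to allow fewer prescriptions, so they may be affected by allocation. Report the unadjusted clustered comparison as support.

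The cost is analysis wording, slightly more analysis work and a small loss of degrees of freedom. All covariates are already recorded before randomisation.

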## Abbreviations

ADA: American diabetes association
cRCT: Cluster randomised controlled trail
CVD: Cardiovascular disease
DA: Decision aid
DE: Design effect
DMP: Disease management programme
EASD: European association for the study of diabetes
EBPI: Evidence-based patient information
EFSD: European foundation for the study of diabetes
GP: General practitioner
ICC: Intracluster correlation coefficient
ICD: International classification of diseases
ISDM: Informed shared decision making
MA: Medical assistant
RCT: Randomised controlled trial
SD: Standard deviation
SDM: Shared decision making
ZI: Central research Institute of ambulatory health care
